### Definition of endpoints

#### Overanticoagulation

Proportion of patient observation time with INR results > 4.5, assuming linear change of INRs.

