## Abstract

**Background:**

The quality control of oral anticoagulant therapy (OAT) during the initiation and maintenance treatment is generally poor. Physicians' ordering of OAT (especially *fluindione *and *warfarin*) can be improved by dose adjustment algorithms, taking into account the results of International Normalized Ratio (INR). Reminders at the point of care, computerized or not, have been demonstrated to be effective in changing physicians prescription behavior.

However, few studies have addressed the benefit of personalized reminders versus non personalized reminders, whereas the personalized reminders require more development to access patient record data and integrate with the computerized physician order entry system.

The Hospital Information System of George Pompidou European Hospital integrates an electronic medical record, lab test and drugs order entry system. This system allows to evaluate such reminders and to consider their implementation for routine use as well as the continuous evaluation of their impact on medical practice quality indicators.

The objective of this study is to evaluate the impact of two types of reminders on overtreatment by oral anticoagulant: a simple reminder of text formatted dose adjustment table and a personalized recommendation for oral anticoagulant dose and next date of INR control, adapted to patient data. Both types of reminders appear to the physician at the moment of drug ordering.

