**Methods:**

The study is an alternating time series experiment with three 6 months periods, each one including every 2 months according to a Latin square scheme: a control period without any reminder, a period with the simple non personalized reminder, a period with personalized reminder. All patients hospitalized in departments using the computerized physician order entry system and ordered *fluindione *or *warfarin*, will be included in the study between November 2004 and May 2006.

Main outcome will be the proportion of overcoagulation, as expressed by the proportion of observation time with INR over 4.5, assuming INR change linearly. Secondary outcome is the incidence of major haemorrhagic events. Data will be collected thanks to Hospital Information Systems databases.

Data will be analyzed taking into account patient and physician clustering effect.

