## Methods

### Experimental design

The study is an alternate time series experiment which consists of three successive six-month periods (timed to change with the changing of medical residents even though they will not be the only prescribers). Each phase will consist of:

• a two-month period without active support during which evaluation criteria will be collected (period A),

• a two-month period with non-personalised active support (period B),

• a two-month period with personalised active support (period C).

To limit the impact of a learning effect on appropriate OAT management practice within the department over time (possible for medical residents), the order of these three periods was determined by using a Latin square plan (see Figure). This experimental design can be considered valid for an impact study in this context whereas a randomised controlled design is difficult to apply with just one hospital [20].

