### Intervention

To prescribe a drug using Dx-Care^®^, the doctor selects the required drug from an exhaustive list. This opens up a dialogue box in which the doctor types the dose, the frequency of intake and the mode of administration. From this window, it is possible to add a text comment or to consult particular protocols that have been defined by the departments.

It is planned to integrate two types of decision support systems into the computerised prescription program:

1) non-personalised active system: when the drug is selected a window automatically opens giving the prescribing the nomogram for the adjustment of OAT doses in the form of a table (see Tables 2 and 3).

2) personalised active system: when the drug is selected a window automatically opens suggesting a dose recommended according to the nomogram (taking into account the doses previously received by the patient and the patient's INR), together with a date for next INR control and an explication.

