### Assessment of evaluation criteria

#### OAT overdose

The Netlab^® ^application allows biological laboratories to receive prescriptions and to return results. All of the INR results can be extracted from the Netlab^® ^database accompanied by information making it possible to identify the patient, the treatment and dose received, the prescribing doctor, the hospitalisation unit, the date the test was prescribed. Data about overdoses can therefore be collected systematically by regular database searches.

Furthermore, the storage of the information in a computerised tool will make it possible to determine previous doses and INR results each time a drug is prescribed.

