### Statistical analyses

Statistical analyses will be performed with the STATA statistical software (release 8, STATA corp, College station, Tex, USA)

Standard statistical tests will be used to compare the baseline characteristics of the departments and patients.

The main analysis concerns the effect of the intervention on the number of dangerously high INRs. The analysis will be carried out using a mixed effect analysis of variance model, in which the effect linked to the period will be considered fixed and that linked to the prescription tool will be considered random [22].

Rosendaal's method will be used to analyse the number of patient-days with INR over the target [21].

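### The main outcome, interpolated time with INR over 4.5, depends on when INRs are drawn, and the personalised tool proposes the next draw date

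*Protocol article*

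**What the plan says.** The endpoint section defines overanticoagulation as "Proportion of patient observation time with INR results > 4.5, assuming linear change of INRs". The Abstract names the same quantity as main outcome: "the proportion of observation time with INR over 4.5, assuming INR change linearly". The Statistical analyses section returns to it: "Rosendaal's method will be used to analyse the number of patient-days with INR over the target".

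The INR values are those ordered in routine care and held in the laboratory database. Under OAT overdose the article states: "Data about overdoses can therefore be collected systematically by regular database searches". It gives no INR schedule common to the three kinds of period.

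The Intervention section says the personalised window suggests a dose "together with a date for next INR control and an explication". The Abstract agrees, describing "a personalized recommendation for oral anticoagulant dose and next date of INR control, adapted to patient data". The non-personalised window shows "the nomogram for the adjustment of OAT doses in the form of a table", and no control date is mentioned for it; the two nomogram tables themselves are not in the text available. Under Experimental design, control periods have no active support.

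**The concern.** Linear interpolation reads time over 4.5 from straight lines between consecutive INRs, so the answer depends on where the lines start and end. If one tool changes when the next INR is drawn, the computed time can change while the patients' true INR paths do not.

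Three routes are possible:

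- **After a high INR.** If the true INR falls quickly and then levels off, a straight line to a late recheck overstates the time over 4.5. An earlier recheck removes some of that excess.
- **Between routine INRs.** Sparse sampling misses peaks, so denser sampling raises the computed time.
- **Who contributes.** A patient with a single INR has no interval to interpolate. A prompt for a recheck can bring such patients into the denominator.

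Both main aims are exposed: the effect of the tools against control, and the advantage of the personalised tool over the non-personalised one. The article contains no step that separates INR timing from INR control.

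**Working it through.** **The plan's own figures.** None is given for the time-based outcome. The sample-size figures concern the share of INR results over 4.5. With p1 = 0.12, p2 = 0.12 × (1 − RRR), two-sided 5%, 80% power and untreated:treated = 1:2, the two-proportion formula gives totals of 2442, 1287, 768 and 495 for RRR 30, 40, 50 and 60%. The stated values are 2500, 1300, 800 and 500, each the computed total rounded up to the next hundred. They reproduce, but say nothing either way on this point.

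**One high INR, one true path.** Interpolated time over 4.5 after a high INR = gap × (INR1 − 4.5) / (INR1 − INR2). Assume an INR of 6.0 falling in a straight line to 2.5 by day 2, then flat.

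- Recheck on day 2: 2 × 1.5/3.5 = 0.86 day, the true value.
- Day 3: 3 × 1.5/3.5 = 1.29 days.
- Day 4: 1.71 days.
- Day 7: 3.00 days.

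The path is the same throughout; only the date of the second INR moves. The overstatement begins once the recheck comes after the fall has levelled off.

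**Whole outcome, unchanged INR process.** The documents give neither INR intervals by period nor the speed of INR change, so all of the following is assumed:

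- log INR is a stationary, mean-reverting process with median INR 2.9 and SD 0.38 on the log scale;
- each patient is observed for 14 days, with 4000 patients per setting;
- true time over 4.5 is about 12%;
- autocorrelation time is 1.5, 3 or 6 days.

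Cells show interpolated share / true share (in %), their ratio, and the change in that ratio against sampling every 3 days.

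| INR schedule | 1.5 days | 3 days | 6 days |
|---|---|---|---|
| Every 3 days | 9.47/12.35 = 0.767 | 10.84/12.89 = 0.841 | 11.13/12.10 = 0.920 |
| 1 day after INR > 4.5, otherwise 3 | 8.48/12.39 = 0.684 (−11%) | 10.00/12.59 = 0.794 (−6%) | 11.80/12.76 = 0.925 (about 0) |
| 1 day after INR > 4.5, otherwise 4 | 7.80/12.39 = 0.630 (−18%) | 8.68/11.98 = 0.725 (−14%) | 11.01/12.49 = 0.882 (−4%) |
| Daily for everyone | 11.20/12.76 = 0.878 (+14%) | 11.37/12.13 = 0.937 (+11%) | 12.01/12.48 = 0.962 (+5%) |

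A rerun with 12,000 patients and the same paths under every schedule gave about 0 to −19% for the two early-recheck schedules and +6 to +14% for daily testing.

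**The two bounds, same rerun.** For an interval with one end over 4.5, the lower bound counts none of it and the upper bound counts all of it. Changes are against 3-day sampling with an unchanged process.

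| Situation | Lower bound | Upper bound |
|---|---|---|
| Early rechecks, INR process unchanged | −3 to +23% | −10 to −24% |
| Early rechecks, true time over 4.5 cut by 30% | −20 to −42% | −35 to −47% |
| Daily for everyone, true time over 4.5 cut by 30% | about +1 to +25% | −36 to −38% |

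With early rechecks alone, the lower bound does not show the fall seen in the upper bound. With a true reduction, both fall. Under much denser general testing the lower bound can rise even though control has improved.

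**The case against.** **Time weighting is the less schedule-sensitive choice.** This stands. In the first simulation, rechecking one day after a high value moved the share of INR results over 4.5 from about 12% to between 16 and 23%, far more than it moved interpolated time. The Statistical unit section also shows awareness of the number of INRs and the time between them. But the dependence is reduced, not removed, and here the timing can differ by the intervention itself.

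**Earlier rechecking may be part of the benefit.** It may. The difficulty is that the outcome could improve even if true INR paths did not.

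**Interval tables and sensitivity analyses belong in a statistical analysis plan.** Their detail does. The problem arises from two things the article fixes: the outcome definition and a tool that proposes INR dates.

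**Stronger readings the documents do not support:**

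- *The tool sets the INR date.* It suggests one; the physician decides.
- *The bias favours the personalised tool.* Its sign is open, since denser testing of everyone works against the tool. A fast-then-flat fall is itself an assumption, and a delayed fall would reverse the overstatement.
- *The artefact could exceed the 30% RRR used for sizing.* A reader might take a peak of 6 falling towards 2 with a one-day half-life: the credited fall is 1.29 days with a recheck on day 3 and 0.75 on day 1, a 42% cut. That covers only the falling limb. Add a rise from 2.5 over three days (3 × 1.5/3.5 = 1.29 days) and the episode goes from 2.57 to 2.04 days, or 21%. The RRR also refers to the share of INR results, a different measure.

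**Conclusion.** The point holds in limited form. The outcome depends on INR timing, only the personalised tool is described as proposing that timing, and nothing in the article separates the two. C versus A is exposed in any case. C versus B is exposed to the extent that the table shown in B gives no control date, which cannot be checked here.

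The shift is about 0 to 19% lower with earlier rechecks after high values and about 5 to 14% higher with denser testing of everyone. These ranges rest on assumed INR gaps of 1 to 4 days and an assumed speed of INR change. The effect is smallest when INR changes slowly relative to the gaps. The documents establish neither its direction nor that it will occur. They establish only that a lower value under the personalised tool could not, by itself, be read as better control. That is worth settling before the periods are compared.

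**What to change.** Keep interpolated time over 4.5 as the main outcome, and add the following before any comparison:

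1. Tabulate by tool the interval between INRs, overall and after an INR over 4.5, and the share of OAT patients and of inpatient days with no usable INR pair.
2. Pre-specify two sensitivity analyses for intervals that cross 4.5: one counts no time beyond the high INR, the other counts all time up to the adjacent INR.
3. State that if INR intervals differ by tool and the direction of effect is not the same under the two bounds, the difference will be reported as possibly due to INR timing and not as shown better control.

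The bounds should not become a test that both must pass. The upper bound is itself sensitive to recheck dates, and the lower bound rises with denser general testing, so a strict rule could hide a real benefit. Their sizes should be read alongside the interval table.

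The cost is slightly more analysis, on INR dates and results already due for extraction and on admission and prescription records in the same hospital system. No new data collection or change to care is needed. The price is a more guarded claim for the personalised tool when the bounds disagree.

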#### Major haemorrhagic accidents

Intra-cranial haemorrhage or spontaneous haemorrhage necessitating surgery or a transfusion or decreasing haemoglobin concentration by more than 2 g/dl.

### Assessment of evaluation criteria

#### OAT overdose

The Netlab^® ^application allows biological laboratories to receive prescriptions and to return results. All of the INR results can be extracted from the Netlab^® ^database accompanied by information making it possible to identify the patient, the treatment and dose received, the prescribing doctor, the hospitalisation unit, the date the test was prescribed. Data about overdoses can therefore be collected systematically by regular database searches.

Furthermore, the storage of the information in a computerised tool will make it possible to determine previous doses and INR results each time a drug is prescribed.

#### Haemorrhagic accidents

When a health care professional decides to declare an undesirable event, he or she fills in a specific, pre-formatted form available on the Intranet. This form includes a list of events that must be declared at the GPEH.

The declaration form includes an item entitled "complication of haemorrhagic accidents". When the doctor clicks on this item, a specific form for the declaration of a haemorrhagic accident associated with anti-coagulant treatment appears (see form in appendix).

### Determination of sample size

The determination of the number of participants necessary requires the definition of the statistical unit of interest, information about the incidence of the evaluation criteria in the study population and a hypothesis about the efficiency of the intervention.

#### Statistical unit

In this study, the main aims are to guide each prescription and to reduce the number of anti-coagulant overdoses: the simplest statistical unit to study is therefore the INR result. This unit will be used to calculate the sample size.

This choice is not, however, perfect and the efficacy results will be presented using other indicators of the quality control of anti-coagulant treatments:

Given the low incidence of major haemorrhagic accidents (not currently measured at the GPEH but probably below 1%), it is not possible in this study to estimate the number of subjects necessary to demonstrate an effect of intervention on the "haemorrhagic accident" endpoint. Recording haemorrhagic accidents will give the frequency of such accidents, which will then be used for realistic estimates of power and sample size if further studies are carried out.

In previous studies evaluating the efficacy of tools to aid the prescription of OAT, the unit considered was not always the same, taking into account the number of INR per patient and the time between INR measurements to greater or lesser extents. The most recent studies considered the number of patient-days according to the method described by Rosendaal [15,16,21]. This method can also be used to calculate the rate of haemorrhagic events as a function of the number of patient-days for a given range of INR values.

We may also carry out an analysis for each prescribing doctor given that the intervention targets doctors directly. This will involve adjusting the effect of the intervention to the fact that intra-physician variability is *a priori *lower than inter-physician variability.

#### Number of INR measurements and predicted frequency of overdoses

During a six-month period (January to June 2004), 4 920 INRs were requested by the six departments which already routinely use the computerized physician order entry system. The frequency of overtreatment can approximately be estimated from the percentage of INR > 4.5 among INR >2. Among the 2620 INR > 2, 330 (12%) were higher than 4.5 (see Table 4). This frequency has been stable during these six months but differed considerably between departments (10% to 23%).

#### Hypothesis about the efficacy of the intervention

The number of INR tests necessary for a six-month period, with an α risk of 5% and a power of 80%, for the comparison of two percentages by classical methods (untreated group half the size of the treated group), for a basal incidence of the judgement criterion of 12% are and for the following hypotheses on relative reduction of the risk (RRR) of overdose, are:

• RRR 30%: 2500

• RRR 40%: 1300

• RRR 50%: 800

• RRR 60%: 500

Carrying out approximately 5000 tests over six months will make it possible to detect an intervention effect of less than 30% in this period. The experimental design includes three six-month periods and should thus ensure adequate power.

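### The stated power is for a comparison of INR test results; it is not shown for the declared main outcome, the share of patient time with INR above 4.5

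*Protocol article*

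**What the plan says.** All references are to the protocol article.

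- **Main outcome.** The abstract's Methods paragraph and the section Overanticoagulation both define it as a share of time. The latter reads "Proportion of patient observation time with INR results > 4.5, assuming linear change of INRs".
- **Unit of the calculation.** The section Statistical unit chooses the single INR result: "This unit will be used to calculate the sample size". It adds that this choice is not perfect and mentions the patient-day method used in more recent studies.
- **Source of the 12%.** The section Number of INR measurements and predicted frequency of overdoses says "The frequency of overtreatment can approximately be estimated from the percentage of INR > 4.5 among INR >2", and then "Among the 2620 INR > 2, 330 (12%) were higher than 4.5".
- **Calculation.** The section Hypothesis about the efficacy of the intervention works "with an α risk of 5% and a power of 80" per cent, "for the comparison of two percentages by classical methods", with the "untreated group half the size of the treated group", and "for a basal incidence of the judgement criterion of 12" per cent. It gives 2500, 1300, 800 and 500 tests for relative reductions of 30, 40, 50 and 60%. It concludes that about 5000 tests in six months detect an effect below 30%, and that three such periods should give adequate power.
- **Analysis.** The section Statistical analyses makes the number of dangerously high INRs the subject of the main analysis and lists Rosendaal's patient-day method separately.

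**The concern.** The calculation presents 12% as the basal value of the main criterion, but it is the basal value of something else. A share of tests and a share of time can differ for three reasons.

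1. **Interpolation.** A single high result occupies only part of the intervals on either side of it. With equally spaced results of 3, 5 and 3, the line is above 4.5 for the last quarter of the first interval and the first quarter of the second. One test in three is high, but only 25% of the time is.
2. **Test frequency.** If a high INR is repeated sooner than a normal one, high values make up more of the tests than of the time.
3. **Denominator.** The 12% is taken among INRs above 2. The outcome, as worded, is a share of all observation time.

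The unit changes as well. A time share is a fraction per patient, and its precision depends on the number of patients and the spread between them. A required number of independent tests does not measure that.

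At stake is a stated design property. A reader would take the sentence about detecting less than 30% in six months as a property of the main outcome, and nothing in the document supports that.

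**Working it through.** **Inputs from the article.** Alpha 5% and power 80% (sidedness not stated; two-sided reproduces the figures). One untreated to two treated. Basal proportion p1 = 0.12. Available: about 5000 INRs per six months (4920 counted, of which 2620 above 2).

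**Step 1. Reproduce the article's figures.** For two proportions with k = 2 treated per untreated, p2 = p1(1 − RRR) and p̄ = (p1 + 2·p2)/3:

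n1 = [1.960·√(1.5·p̄(1 − p̄)) + 0.842·√(p1(1 − p1) + p2(1 − p2)/2)]² / (p1 − p2)², total = 3·n1.

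For RRR 30%: p2 = 0.084, p̄ = 0.096, p1 − p2 = 0.036. The two terms in the bracket are 0.7072 and 0.3195, so n1 = (1.0266/0.036)² = 813 and the total is 2440.

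| RRR | Computed total | Stated |
|---|---|---|
| 30% | 2440 | 2500 |
| 40% | 1286 | 1300 |
| 50% | 767 | 800 |
| 60% | 492 | 500 |

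Each stated figure is the computed one rounded up to the next hundred. The arithmetic is sound, and it identifies the calculation as a comparison of independent INR tests. On that basis, 5000 tests at 12% detect a reduction of 21.5% with 80% power. If only the 2620 tests above 2 are counted, to which the 12% applies, the figure is 29.0%.

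**Step 2. Trace the 12%.** 330/2620 = 12.6%, a share of tests above 2. Over all INRs it is 330/4920 = 6.7%. Neither is a share of time, and no section converts one to the other.

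**Step 3. Sensitivity to the basal value (assumed; the article gives no time share).** Same formula, RRR 30%:

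| Assumed basal value | Units needed | Against about 5000 |
|---|---|---|
| 12% | 2440 | fewer |
| 8% | 3796 | fewer |
| 7% | 4377 | fewer |
| 6% | 5152 | more |
| 5% | 6237 | more |

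The crossing point is at about 6.2%.

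**Step 4. How a 12% test share could map to time (assumption).** If time above 4.5 is tested m times as densely as other time, the time share is 0.12/(0.88·m + 0.12). For m = 1.5, 2 and 3 this gives 8.3%, 6.4% and 4.3%, and the formula then needs about 3630, 4830 and 7210 units. The article gives no retest intervals, so m is unknown.

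**Limit of steps 3 and 4.** They still treat the outcome as independent yes/no tests. They show that the requirement depends heavily on the basal value; they are not power for a time share. That would need the basal time share and its between-patient SD, and the article gives neither.

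**The case against.** **The proxy is disclosed.** The article says that the INR unit is imperfect and that the frequency is only approximately estimated. This stands, and nothing is concealed. But the caveat supplies no conversion, and the calculation then drops it: the proxy is named as the criterion and the conclusion carries no qualification.

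**The main analysis may be on INR counts.** The section Statistical analyses puts the number of high INRs first. If the authors keep that as the main criterion, a test-based calculation is of the right kind and the mismatch largely disappears. This also stands. The point therefore depends on a conflict within the article that has to be settled first, and the fix must allow for either outcome.

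**Stronger readings that the document does not support.** A reader might infer that the six-month claim is false, or that the study is underpowered. Neither follows. By the article's own formula, the 30% scenario still fits within 5000 units at basal values of 7% or 8%, and fails only at about 6% or below. The conclusion of adequate power rests on all three periods. With about 15000 tests the same formula gives about 97% power for a 30% reduction even at a 4% basal value, before any allowance for clustering by patient or physician. A patient-level detectable reduction would need a mean, an SD and a number of patients, all of which would have to be assumed, so no figure is offered. Nor does any section plan to draw conclusions from a single six-month phase.

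**Conclusion.** The point holds as a mismatch that is never bridged. The 12% is the share of INR results above 2 that exceed 4.5, the formula compares independent tests, and the declared main outcome is a share of patient time. The stated power is therefore not shown for that outcome, and calling the 12% the basal value of the judgement criterion is wrong as long as the time share is the main outcome.

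The four sample-size figures are correct for what they compute. How far they are off for the time outcome cannot be determined from the document. The illustrative range for a 30% reduction (about 3800 units at 8% to 6240 at 5%, against 2440 at 12%) rests on assumed basal values and on a formula that does not strictly apply to a time share. The six-month statement is unsupported for the main outcome; it has not been shown to be false.

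**What to change.** 1. Reconcile the abstract, the section Overanticoagulation and the section Statistical analyses on one main criterion.
2. Relabel the 12% as the share of INR results above 2 that exceed 4.5.
3. If the time share is kept, apply Rosendaal's method to the January to June 2004 INR data. Take the basal time share and its between-patient SD from it, and restate the detectable reduction per six-month phase and over 18 months. This assumes that patient-linked, dated results can be extracted for that period, as the section OAT overdose suggests.
4. Until that is done, or if the INR count is kept, state that the four figures and the sentence on detecting less than 30% apply only to the INR-test proportion.

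The cost is a small re-analysis and a rewritten paragraph. The stated detectable effect may become less favourable. No added enrolment is needed.

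### The power statement sets a requirement based on INRs above 2 against a count of all INRs, so one semester has almost no reserve for a 30% reduction

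*Protocol article*

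**What the plan says.** Under Number of INR measurements and predicted frequency of overdoses, the protocol article gives the volume for January to June 2004: "4 920 INRs were requested by the six departments" already using computerised order entry. It then defines the base rate: "The frequency of overtreatment can approximately be estimated from the percentage of INR > 4.5 among INR >2". The figures are: "Among the 2620 INR > 2, 330 (12%) were higher than 4.5".

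Under Hypothesis about the efficacy of the intervention, 12% becomes the base incidence. With 5% alpha, 80% power and the "untreated group half the size of the treated group", the article lists 2500, 1300, 800 and 500 tests for relative reductions of 30%, 40%, 50% and 60%. It concludes: "Carrying out approximately 5000 tests over six months will make it possible to detect an intervention effect of less than 30% in this period". It adds that, because there are three such periods, power should be adequate.

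Three other statements bear on this. The Statistical unit section takes the single INR result as the unit for sample size and calls that choice imperfect. The Abstract says the analysis will allow for clustering by patient and by physician. The section with the 2004 figures reports that the rate varied from 10% to 23% between departments.

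**The concern.** The requirement and the supply are counted on different bases. The 2500 follows from a rate that exists only among INRs above 2, of which a semester yields 2620. The figure it is compared with, about 5000, matches INRs of every value. At 12%, 5000 tests would contain 600 results above 4.5 (5000 × 0.12); the article's own six-month data contain 330.

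The mismatch makes one semester look as if it has a large reserve. That reserve is what would have absorbed repeated INRs within patients and prescribers, for which the sample size makes no allowance. The statement about the whole study is then built on the semester figure.

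**Working it through.** **Inputs from the protocol article.** Alpha 5% (sidedness not stated; two-sided reproduces the list, one-sided does not), power 80%, untreated to treated 1:2, base rate 12%. Six-month counts: 4920 INRs, 2620 above 2, 330 above 4.5. Three semesters.

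**Formula.** With r = 2, p2 = p1 × (1 − RRR) and p̄ = (p1 + r·p2)/(1 + r):

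n(untreated) = [1.96·√((1 + 1/r)·p̄(1 − p̄)) + 0.8416·√(p1(1 − p1) + p2(1 − p2)/r)]² / (p1 − p2)², and total = 3n.

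**Reproducing the stated figure.** For a 30% reduction, p1 = 0.12, p2 = 0.084 and p̄ = 0.096. The two terms are 0.7072 and 0.3195. Their sum squared, 1.054, divided by 0.036² gives n = 813 and a total of 2440 (2563 with continuity correction), against the stated 2500. For 40%, 50% and 60% the uncorrected totals are 1286, 767 and 492, against 1300, 800 and 500. The method is identified.

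**One semester on each base, 30% reduction.** The two rates other than 12% are 330/2620 = 12.6% and 330/4920 = 6.7%. Paired values are without / with continuity correction; power is uncorrected.

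| Base | Needed | Available | Available ÷ needed | Power | Detectable reduction |
|---|---|---|---|---|---|
| As paired in the text: 12%, all INRs | 2440 / 2563 | 5000 | 2.05 / 1.95 | 97.8% | 21.5% / 21.8% |
| INRs above 2, 12% | 2440 / 2563 | 2620 | 1.07 / 1.02 | 82.6% | 29.0% / 29.7% |
| INRs above 2, 12.6% | 2311 / 2429 | 2620 | 1.13 / 1.08 | 84.5% | 28.3% / 29.0% |
| All INRs, 6.7% | 4580 / 4801 | 4920 | 1.07 / 1.02 | 82.6% | 29.0% / 29.7% |

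The three consistent rows agree closely, so the result does not depend on which base was meant. The number of INRs from patients actually on oral anticoagulants is not given. With the 330 high values fixed, its position between 2620 and 4920 makes little difference.

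**Clustering (assumed).** The article gives no design effect. With DE = 1 + (m − 1)·ICC, an assumed 5 to 10 INRs per patient and ICC of 0.1 to 0.3 give 1.4 (1 + 4 × 0.1) to 3.7 (1 + 9 × 0.3). Dividing the counts by DE, at 12%, pooled active against control:

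| Design effect | Power for 30%, one semester (2620) | Power for 30%, 18 months (3 × 2620 = 7860) | Detectable reduction, 18 months |
|---|---|---|---|
| 1 | 82.6% | 99.9% | 17% |
| 1.5 | 66.5% | 98.2% | 21% |
| 2 | 54.7% | 94.2% | 24% |
| 3 | 40.3% | 82.6% | 29% |
| 4 | 32.2% | 71.4% | 33% |

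**The case against.** The best defence is that the quoted sentence survives. It promises detection of an effect below 30%, and on any consistent base the detectable reduction is 28 to 30%. A reader might infer that the sentence is false; under the article's own independent-INR method it is not. Nor does the article state a two-fold margin or a 21.5% detectable effect. Those follow from setting 5000 beside 2500, and they should not be attributed to the sponsor as claims.

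Second, the article rests its conclusion on power on three semesters. With 7860 INRs above 2 against about 2440 needed, the ratio is 3.2, and 80% power for 30% holds up to a design effect of 3.

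Third, the low single-semester figures come from assumed clustering, not from the denominator. The denominator alone lowers power from about 98% to about 83%. The design effect could also be smaller than a simple formula suggests, since residents work through all three tool periods of a semester and part of the prescriber variation may cancel.

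Fourth, 2620 per semester is a 2004 count from six departments, and the article says use of the order entry system is still growing, so the true volume may be higher.

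All four points stand and limit the consequence. They do not remove the mismatch, and they do not answer the lack of a clustering allowance in the sample size: the Abstract's commitment covers the analysis only.

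**Conclusion.** The error is established: rate and count are on different denominators. Corrected, one semester offers 1.02 to 1.13 times the tests needed for a 30% reduction, with power of about 83 to 85% and a detectable reduction of about 28 to 30%. No single break-even design effect should be quoted, because the reserve depends on rounding of the base rate and on the continuity correction.

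The single-semester claim is true only narrowly and only under independence. Any design effect above roughly 1.02 to 1.13 takes it below 80% power, and the protocol itself expects clustering. How far below rests on assumed design effects.

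A reader might go on to infer that the trial is underpowered. The documents do not support that for a 30% reduction over 18 months: if the 2004 volume continues, power falls below 80% only at a design effect somewhat above 3. This should be corrected, but it does not undermine the design.

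**What to change.** Put the rate and the count on one base: 12.6% of 2620, or 6.7% of 4920. Drop the single-semester claim, or qualify it as valid only if INRs are independent. Base the power statement on the 18-month total, labelled as pooled active against control and as assuming the 2004 volume. The detectable reduction is then about 17% if INRs were independent, and about 24%, 29% and 33% for assumed design effects of 2, 3 and 4. If the hospital database can supply INRs per patient and the within-patient correlation, use those in place of the assumed range.

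The cost is a less favourable stated figure and a few rewritten sentences. No patients are added, and study length and design do not change.
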